## Biological sampling procedures

### Handling, storage, and destruction of biological samples

Three vaginal forceps biopsies of 3-4 mm will be taken at Visit 2 and Visit 4 after local anesthesia. One biopsy will be fixed in formalin and used for pathophysiological examination and immunohistochemical (IHC) analysis. A second biopsy will be placed in RNA*later* RNA Stabilization Reagent (Qiagen) and subjected to RNA isolation and gene expression analysis. The third biopsy will be used to study biofilm formation. The laboratory work will be performed at the core facilities at Karolinska Institutet.

### Total volume of blood per subject

N/A

### Biobank

All biopsy samples taken in this study will be registered in “Stockholm medical biobank” (register number 914, sample ID Bb142563) and handled according to the current biobank laws and regulations. The samples are coded/pseudonymized to protect the subject´s identification. All samples and the identification/code list are stored securely and separately to prevent unauthorized persons from having access to them.

## End of Study

The study ends when the last subject has completed the last follow-up. The study may be prematurely terminated if it appears that the treatment involved a large number of serious adverse events (SAE) or if recruitment of subjects cannot be met within reasonable time limits. If the study is prematurely terminated or suspended, the investigator should immediately inform the subjects about this and ensure appropriate treatment and follow-up. The regulatory authority should be informed as soon as possible, but no later than within 15 days.

Decisions on premature termination are taken by the sponsor.

# Subject selection

## Inclusion criteria

To be included in the study, subjects must meet the following criteria:

- 18-50 years of age
- A history of > 2 candida infections the last year
- Symptoms of acute vulvovaginal candida infection
- Culture verified infection with *Candida albicans*
- Adequate contraceptive method
- Able to understand oral and written information in Swedish
- The subject has given written consent to participate in the study

## Exclusion criteria

Subjects must not be included in the study if any of the following criteria are met:

- Severe somatic or mental illness (including liver and kidney failure and cardiac disease)
- Immunosuppressive medication
- Pregnancy
- Lactation
- Other ongoing gynecological infections
- Allergy to fluconazole or chlorhexidine gluconate
- Citalopram or other medication that might have impact on the QT interval (terfenadin, cisaprid, astemizol, pimozid, kinidin, erythromycin, halofantrin, amiodaron)
- Participation or recent participation (30 days) in a clinical study with an investigational product. Previous participation in this study.

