Many women with RVVC are referred to the vulvar clinic at the gynecological department at Danderyd Hospital in Stockholm. We have followed these women clinically for many years and have also performed several scientific studies. Our clinical experience is fully in line with the described high risk of infection relapse and the need for repeated and long use of fluconazole. Several of our patients have problems with side effects of the medication and there are also difficulties in combining fluconazole with other concomittant medications commonly used by this group of patients. If Hibitane® is at least as effective as fluconazole with little impact on vaginal lactobacillus, with high tolerablility and without cytotoxic effect on epithelial cells, the results of the study might lead to that an already established and inexpensive drug can be used by a large group of young women with a new indication.

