## Procedures and flow chart

**Five research visits are planned:**

**Visit 1** Screening – oral and written study information, signing of informed consent, vaginal culture for Candida albicans and chlamydia/gonorrhea (PCR test). 45 min.

**Visit 2** Inclusion (baseline), within 1 week after Visit 1. Control for inclusion/exclusion criteria, randomization to study medication after positive culture for *Candida albicans* and negative chlamydia/gonorrhea (PCR test) – health survey, control of concomitant medications, examination, vaginal biopsies, pregnancy test and control of adequate contraceptive methods to avoid pregnancy throughout the study. 1 h.

**Visit 3** 1 week (+2 days) after completed treatment. Control of AE, culture for *Candida albicans* and examination (no biopsies). 30 min.

**Visit 4** After 12 weeks (+ 1 week) from inclusion when prophylactic treatment is completed. Control of AE and relapses, culture for *Candida albicans* and examination, vaginal biopsies. 45 min.

**Visit 5** Follow-up 6 months (+ 1-2 weeks) from baseline/inclusion. Control of AE and relapses, culture for *Candida albicans* and examination (no biopsies). End of study. 30 min.

A weekly web-based dairy (eCRF (Entermedic)) will be used for follow-up of treatment

compliance, efficacy and adverse events. A personal link will be sent via e-mail every week

from week 2-24. During the prophylactic treatment (Visits 2-3) and during the observational

phase of the study (Visit 4-5), the participants are asked to report any suspicious relapses in

the dairy and contact the research midwife if needed. They will also receive equipment for

vaginal cultures that can be used for self-sampling at home to detect true relapses. In case of

positive cultures for *Candida albicans*, they will be offered the same medication as previously

used in the study if the treatment was effective and no adverse events occurred. Otherwise,

an individual treatment option will be used.

Table 1 Flow chart

| **Procedure** | **Visit 1**  Screening  Week -1 | **Visit 2**  Baseline/  inclusion  Week 0  (within 1 w from Visit 1) | **Visit 3**  Follow-up  Week 1  (treatment)  (+2 d) | **Visit 4**  Follow-up  Week 12  (prophylactic phase)  (+1 w) | **Visit 5**  Follow-up  Week 24  (observational phase)  (+2 w) |
| --- | --- | --- | --- | --- | --- |
| Incl/exclusion criteria | √ | √* |  |  |  |
| Informed signed consent | √ |  |  |  |  |

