**Fluconazol®, oral capsules 150 mg**

Most participants are probably already familiar to the fluconazole regime since they suffer from recurrent candida infections. The capsules come in paper packaging of 6 capsules in each. A total of 18 capsules will be prescribed, but additional prescriptions might be needed if the infection relapses. The packaging is marked at the pharmacy and can be kept at room temperature (< 30° C). The capsules should be administered approximately at the same time every day.

A written information of the fluconazole administration is provided.

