## Concomitant medications

Medications that are considered necessary for the safety and well-being of the subject can be given at the discretion of the investigator, unless otherwise specified as an exclusion criterion. Concomitant medications are reported in the CRF.

If treatment fails (positive culture for *Candida albicans* and symptoms), rescue medication of vaginal Clotrimazole 200 mg twice per week will be provided in both study groups for the rest of the study period. The regime of Clomitrazole is another established treatment for vulvovaginal *Candida albicans* infection.

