## Sample size calculations

The sample size and calculated power for the primary outcome of negative cultures for *Candida albicans* is based on data in Alvendal et al. Acta Obstet Gynecol Scand. 2017. In that study there was 100% positive cultures for *Candida albicans* before routine treatment with fluconazole for RVVC. After fluconazole treatment, 14% participants were still culture positive, with 86% success rate of primary outcome. Using the presumption: α= 5% β= 90%, success for routine FLZ treatment= 86%, success for experimental treatment with CHG in the current study= 86% with non-inferiority limit= 30%, 46 participants are needed (23 in each group) to achieve a power of 90 % not to exclude an effect-size of 30%. 60 participants will be included in case of drop-outs. All test will be performed at the 5% significance level.

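### Entry criteria do not restrict current, recent or between-visit antifungal use, so fluconazole carried into the CHG arm can bias the comparison toward non-inferiority

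*Protocol*

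**What the plan says.** **Eligibility (Protocol 6.1, 6.2 and synopsis).** Entry needs more than two candida infections in the last year, acute symptoms and a culture positive for *C. albicans*. On fluconazole, the exclusions are "Allergy to fluconazole or chlorhexidine gluconate" and drugs that affect the QT interval. The only time window is 30 days, and it concerns investigational products in clinical studies. No criterion mentions current or recent antifungal treatment.

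**Visits (Protocol 5.2 and Table 1).** The Candida culture is taken at Visit 1. Visit 2, where women are randomised, follows within a week and has no Candida culture. It does include "health survey, control of concomitant medications", and the entry criteria are checked again, but no criterion tells the investigator to act on an antifungal.

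**Other medication (Protocol 7.8).** Medication judged necessary for the woman's safety and well-being "can be given at the discretion of the investigator, unless otherwise specified as an exclusion criterion". Antifungals are not so specified.

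**Population.** The Background and rationale describes the clinic's patients in terms of relapse and "the need for repeated and long use of fluconazole". The section on the fluconazole capsules says: "Most participants are probably already familiar to the fluconazole regime since they suffer from recurrent candida infections".

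**Benchmark (Protocol 10.4).** The comparator rate comes from an earlier study in recurrent candidiasis: "After fluconazole treatment, 14% participants were still culture positive, with 86% success rate of primary outcome". The non-inferiority limit is 30 percentage points.

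**The concern.** The trial asks whether CHG alone clears the infection about as often as fluconazole. A woman who took fluconazole shortly before randomisation and is allocated CHG is in effect treated with both. If she clears because of the earlier drug, she counts as a CHG success. In the fluconazole arm the same prior dose adds little, because every woman there receives the drug anyway. Randomisation balances prior use between the arms, but it cannot remove an effect that acts mainly in one of them. Intention-to-treat analysis does not remove it either.

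In a superiority trial this contamination would usually work against the new treatment. In a non-inferiority trial it narrows the gap and makes a positive conclusion easier to reach. The wait of up to a week between a positive culture and randomisation, in women with symptoms who know the drug, is a plausible time for it to happen. Eligibility is fixed by the protocol, so an analysis plan cannot repair this afterwards.

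**Working it through.** **1. Inputs.** From Protocol 10.4: "Using the presumption: α= 5% β= 90%, success for routine FLZ treatment= 86"% (the 90% is the power), CHG success also 86%, limit 30 points, 23 per arm needed, 60 women enrolled. Allocation is 1:1 (Protocol 7.5), so 30 per arm. Not in the documents, hence assumed: the share g of the CHG arm affected by carry-over, and the clearance in those women.

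**2. The plan's own figure.** n per arm = (z₁₋α + z₀.₉₀)² × [0.86×0.14 + 0.86×0.14] / 0.30².
- One-sided α = 5%: (1.645 + 1.282)² × 0.2408 / 0.09 = 22.9, so 23 per arm and 46 in total. This agrees with the Protocol.
- One-sided α = 2.5%: 28.1, so 29 per arm and 58 in total. This does not agree.

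The stated size therefore corresponds to a one-sided 5% test. Because a 95% confidence interval is also planned (10.2.1), both are shown below.

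**3. Method.** Set true CHG clearance without carry-over to 86% − 30 points = 56%, exactly at the limit, so that a declaration of non-inferiority is an error. Enumerate all outcomes of two binomials with n = 30. Declare non-inferiority when the lower Wald limit for CHG minus fluconazole lies above −30 points.

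**4. Carry-over.** A share g of the CHG arm is assumed to clear at the fluconazole rate: CHG rate = 0.56(1 − g) + 0.86g.

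| g | CHG rate | Apparent gap | False non-inferiority, one-sided 5% | 95% CI |
|---|---|---|---|---|
| 0 | 56% | 30 points | 5.0% | 2.7% |
| 10% | 59% | 27 points | 8.5% | 4.9% |
| 20% | 62% | 24 points | 13.7% | 8.6% |

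Cross-check by normal approximation for g = 10%: SE = √[(0.86×0.14 + 0.59×0.41)/30] = 0.110; Φ[(0.30 − 0.27)/0.110 − 1.645] = 8.5%. For g = 20% it gives 13.7%.

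**5. Breakthrough on fluconazole.** Suppose 20% of entrants are refractory and clear at 40% on fluconazole. The comparator becomes 0.8×86% + 0.2×40% = 76.8%. What follows depends on how these women do on CHG:

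| CHG clearance in refractory women | CHG rate | Gap | One-sided 5% | 95% CI |
|---|---|---|---|---|
| 56%, unaffected | 56% | 20.8 points | 18.8% | 11.8% |
| 40%, same as on fluconazole | 52.8% | 24 points | 12.1% | 7.1% |
| 10%, same 46-point loss as on fluconazole | 46.8% | 30 points | 4.4% | 2.3% |

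The gap narrows only if refractoriness costs fluconazole more clearance than it costs CHG. With equal losses there is no inflation.

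**The case against.** **Carry-over is partly guarded against.** Entry needs symptoms and a positive culture, so a drug taken before Visit 1 had not cleared the infection by then. Criteria and medication are reviewed at Visit 2, and an antifungal that worked between visits might remove the required symptoms. Section 7.8 covers medication judged necessary for the woman and is not a blanket permission. All of this stands and limits the route, mainly to recent or between-visit dosing. It does not close it. A dose just before Visit 2 need not have removed symptoms by then, the culture is not repeated, and no rule makes such a woman ineligible.

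**The size is not known.** Being familiar with fluconazole, or needing it repeatedly, is not the same as taking it at entry. This stands. The rates in the working are a range under assumptions, not estimates for this trial.

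**A reader might infer more: that the criteria enrol fluconazole failures and so depress the comparator.** The documents do not support stating this as fact. They give no share of refractory women, and the Background reports no major resistance problem so far. The 86% comes from women on routine treatment for recurrent disease and may already include prior users. In the illustration with CHG unaffected, the true gap among the women enrolled is 20.8 points, inside the limit, so non-inferiority would be correct for that population. It would be an error only against a fluconazole-responsive group, which the Protocol does not name as its target. Whether to enrol women with breakthrough is a choice of target population, and they may be among those for whom an alternative matters most.

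**Conclusion.** The gap is real but moderate. As written, the Protocol lets a woman be randomised with fluconazole or another antifungal still acting, and in the CHG arm this can bias the primary comparison toward non-inferiority. If 10% to 20% of the CHG arm clear at 86% for that reason, the false non-inferiority rate goes from 5.0% to between 8.5% and 13.7% (one-sided 5%), or from 2.7% to between 4.9% and 8.6% (95% interval). This assumes 30 evaluable women per arm, CHG truly at 56%, fluconazole at 86% and a Wald interval. A smaller share, or only partial benefit from the earlier drug, gives a smaller effect.

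A lower comparator rate through breakthrough cases is possible but conditional, and is no ground for requiring their exclusion. The sample size of 46 reproduces and is not in dispute here. The point is a cheap improvement, not a fatal flaw.

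**What to change.** 1. Add to the exclusion criteria in 6.2 and in the synopsis: current antifungal treatment; any antifungal, oral or vaginal, within a period before the Visit 1 culture that the sponsor defines; and any antifungal between Visit 1 and randomisation.
2. Check this at Visit 2 with the medication control already done there.
3. Align 7.8, so that its reference to the exclusion criteria covers these antifungals.
4. Record prior fluconazole exposure and breakthrough on fluconazole at baseline, so that the primary result can also be reported by them.

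The cost is a few lines of text, one baseline item and somewhat slower recruitment. No added visit or culture is needed, and the stated sample size does not change.

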## Screening

Subject eligibility (that subjects fulfill all inclusion criteria and do not meet any exclusion criteria) is established before inclusion, treatment, or randomization.

## Withdrawal criteria

Subjects can discontinue their participation in the study at any time without any consequence to his/her continued treatment. The investigator/sponsor can at any time terminate the study for a subject due to, e.g., unacceptable adverse events/adverse reactions or because the subject does not follow procedures in the study protocol. If the subject discontinues the study, follow-up of this subject will be performed according to the clinic’s routine.

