## Overall study design

The study is a 6 months clinical Phase II trial to compare if 1% chlorhexidine gluconate vaginal cream (Hibitane®) is at least as effective and safe as fluconazole (reference treatment) for culture-verified recurrent vulvovaginal candidiasis. The study is a randomized open non-inferiority trial with parallel treatment groups. The trial is not possible to blind for neither participants nor investigators due to the differences between study treatments. There is low risk of bias since the primary outcome variable is objective (negative vaginal culture for *Candida albicans*).

The rational for the study is to find an alternative treatment to fluconazole for RVVC with high tolerability and without cytotoxic effect on epithelial cells and negative impact on the vaginal microbes.

The participants will be randomization to;

- Investigational medication with Hibitane® vaginal cream 8 ml every night for a week and then prophylactic treatment with 8 ml/week for another 11 weeks

or

- Reference treatment with Fluconazole® 150 mg (oral capsule) every 3 days for the first 3 doses, then prophylactic treatment with 150 mg/week for another 11 weeks

Please see section 7 for more details on randomization and study treatments.

Figure 1 Study design

| **Visit** | **1** | **2** | **3** | **4** | **5** |
| --- | --- | --- | --- | --- | --- |
|  |  | CHG | Chlorhexidine gluconate  vaginal application  8 ml/w, 11 w | |  |
|  |  | 8 ml/day,1 w  R |  |  | N=30 |
|  |  |  | Fluconazole  oral capsules  150 mg/w, 11 w | |  |
|  |  | FLZ  150 mg/day,1w |  |  | N=30 |
| **Week:** | **-1** | **0** | **1** | **12** | **24** |
|  | Screening | Inclusion/  Baseline  Randomization | Follow-up | Follow-up | Follow-up and end of treatment |

##

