# Study treatments

## Description of investigational product(s)

The study participants will be randomization to either;

1. **Hibitane®** (investigational treatment), manufactured by Bioglan AB, [name]. 1 ml contains 10 g chlorhexidine gluconate (1%) and 20 mg Cetostearyl alcohol.

Therapeutic indications: anti-septic use for clinical vaginal examinations, especially during delivery.

Administration time: 3 months with additional treatment in case of infection relapse during the observational phase of the study, 3-6 months after inclusion.

Known adverse event: irritation on skin and mucosa.

Restrictions: allergy to the active substance, avoid contact of active substance with brain or meningeal tissue, or ear canal due to neurotoxicity. Hibitane® is approved for vaginal use even during pregnancy and lactation

or

1. **Fluconazole** (control or standard treatment), manufactured by different producers. Oral capsules of 150 mg fluconazol + 139 mg laktos.

Therapeutic indications: different types of fungal infections (cryptocock meningitis, coccidioido mycosis, invasive candidiasis) including mucosal Candia albicans infections.

Administration time: 3 months with additional treatment in case of infection relapse during the observational phase of the study, 3-6 months after inclusion.

Known adverse events: most common side effects are; headache, abdominal pain, nausea, vomiting, diarrhea, skin rashes. For more information, see attached product resume.

Restrictions: allergy to the active substance, doses should be adjusted in case of reduced renal or liver function, concomitant use of medications with known risk of increasing QT-interval and be metabolized via cytocrom P450 (CYP)3A4 (cisaprid, astemizole, pimozid, quinidine and erythromycin). Fluconazole is not approved during pregnancy. For more information, see attached product resume.

Both medication will be prescribed and handled routinely by the pharmacies.

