## Reporting and registration of Adverse Events

At each study visit, adverse events (AE) are continuously registered, starting from start of treatment with the investigational products, up to and including 12 weeks after the subject has ended their treatment with the investigational products. All AE that occur during the study and which are observed by the investigator/study midwife or reported by the subject will be registered in the CRF regardless of whether they are related to the investigational product or not. Assessment of causal relationship, severity, and whether the AE is considered to be an SAE or not will be done by the investigator directly in the *CRF*. The subjects can also report AEs in the digital weekly diary or via communication with the investigator/study midwife. At minimum, for each AE/SAE, a description of the event is recorded (diagnosis/symptom if diagnosis is missing), start and stop dates, causal relationship, severity, if the AE is considered to be an SAE or not, measures and outcome. These data will also be reported in the participant’s medical record.

All reported new symptoms in both study groups will be evaluated as a possible AE.

All AE shall be registered in the CRF from start of treatment to 12 weeks after end of prophylactic treatment *as above (section 9.3, Reporting and registration of Adverse Events)*.

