### Drop-outs

Differences in drop-out rates across treatment arms and baseline characteristics will be analyzed using Mann Whitney U test. Efficacy and safety will be analyzed for all randomized patients (i.e. intent-to-treat ITT). Additionally, we will also examine efficacy for the per-protocol (PP) population. We will examine the difference in dropout rates and missing visits across treatment arms.

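### Women removed from the study for adverse events or non-adherence keep no study visits, so their later data are lost; separately, Section 9.3 gives two different ends to adverse event registration

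*Protocol*

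**What the plan says.** **Removal and follow-up.** Protocol Section 6.4 (Withdrawal criteria) states: "The investigator/sponsor can at any time terminate the study for a subject due to, e.g., unacceptable adverse events/adverse reactions". Failure to follow protocol procedures is a second ground. The section ends: "If the subject discontinues the study, follow-up of this subject will be performed according to the clinic’s routine".

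**Related provisions.** Section 7.2 allows a dose change or withdrawal of the medication for an adverse event. Section 9.4 lists dose adjustment, treatment interruption and study withdrawal as possible measures, and follows women with an adverse event until it is resolved or stable. Section 7.8 provides rescue medication after treatment failure for the rest of the study period.

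**Analysis.** Section 10.2.2 says: "Efficacy and safety will be analyzed for all randomized patients". Section 8.2 analyses adverse events as the proportion of women with one.

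**Adverse event registration.** Section 9.3 gives two end points: "up to and including 12 weeks after the subject has ended their treatment with the investigational products", and later "from start of treatment to 12 weeks after end of prophylactic treatment".

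**Re-treatment and last contact.** Section 7.1 allows, in both arms, "additional treatment in case of infection relapse during the observational phase of the study, 3-6 months after inclusion". Section 5.2 offers the same drug again only if it worked and caused no adverse event. It places Visit 5 at 6 months (plus 1 to 2 weeks) as the end of the study, and the weekly diary stops at week 24. Figure 1 labels week 24 "Follow-up and end of treatment".

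**The concern.** Stopping study drug and leaving the study are different events, and only the second needs to end data collection. Section 6.4 makes intolerance and non-adherence grounds for ending participation, and then hands follow-up to routine care. The plan would thus stop measuring women because of what happened to them on treatment, while promising to analyse everyone randomised. An analysis plan can say how missing outcomes are handled; it cannot recover cultures, smears or biopsies that were never taken.

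This touches questions the trial is meant to answer. Irritation of skin and mucosa is the known adverse event of the cream (Section 7.1). Epithelial toxicity is judged from biopsies at Visits 2 and 4 only, and lactobacilli at Visits 2 to 5 (Table 1). The trial is open, and the investigators who conduct the visits can also end participation.

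The two ends of adverse event registration are a separate matter. They agree for a woman whose last dose is at week 12, but diverge once study drug is given again in months 3 to 6.

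**Working it through.** **1. What is lost, by time of removal (Table 1, Sections 5.2 and 6.4)**

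| Removed | Scheduled study data lost |
|---|---|
| Before Visit 3 | Primary culture; all later cultures, scores and smears; Visit 4 biopsy; relapse data; new adverse events |
| Between Visits 3 and 4 | 3- and 6-month cultures, scores and smears; Visit 4 biopsy; relapse data; new adverse events |
| Between Visits 4 and 5 | 6-month culture, scores and smear; later relapses; new adverse events |

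Removal after Visit 3 cannot change the primary endpoint. Removal at any time before Visit 4 costs the only post-treatment biopsy.

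**2. The plan's own sample size (Section 10.4)**

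Inputs: success 86% in both arms, limit 30 points, power 90%.

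n per arm = (z_alpha + z_power)² × [p1(1-p1) + p2(1-p2)] / limit²

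One-sided 5%: (1.645 + 1.282)² × (2 × 0.86 × 0.14) / 0.30² = 22.9, so 23 per arm and 46 in all, as stated. One-sided 2.5% would need 29 per arm. Randomising 60 allows for a loss of (60 - 46)/60 = 23.3%; the protocol gives no expected rate.

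**3. Illustration for the primary endpoint**

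Assumptions, none of them from the protocol: fluconazole 26/30 clear, chlorhexidine truly 22/30 clear, all early removals are chlorhexidine failures, and only observed cultures are analysed.

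Lower limit = (p_CHG - p_FLZ) - 1.96 × √[p_CHG(1-p_CHG)/n_CHG + p_FLZ(1-p_FLZ)/n_FLZ]

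| Failures removed before Visit 3 | CHG observed | Difference (points) | Wald 95% lower limit | Newcombe | 30-point limit |
|---|---|---|---|---|---|
| 0 | 22/30 | -13.3 | -33.3 | -32.8 | missed |
| 2 | 22/28 | -8.1 | -27.6 | -27.9 | met |
| 4 | 22/26 | -2.1 | -20.5 | -21.9 | met |

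First row: -0.1333 - 1.96 × √(0.00652 + 0.00385) = -0.1333 - 0.1996 = -0.333.

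In terms of error rates (normal approximation, one-sided 5%): suppose true chlorhexidine success is 56%, exactly at the limit, and all removed women are failures. Leaving out 10% or 20% of that arm raises its observed success to 0.56/0.9 = 62.2% or 0.56/0.8 = 70%. The chance of a false non-inferiority conclusion rises from 5% to 13.7% or 34.3%.

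Counting missing as failure works the other way. With true success 86% in both arms and 10% early loss from chlorhexidine alone, counted success is 0.86 × 0.9 = 77.4%, and power falls from 95.6% (30 per arm) to 69.6%.

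**4. The two adverse event windows (Section 9.3)**

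Window tied to the end of investigational product = week of last dose + 12. Last contact is week 24, at latest week 26.

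| Last study-drug dose | Window closes | Weeks past week 24 | Weeks past week 26 |
|---|---|---|---|
| Week 12 (no re-treatment) | 24 | 0 | 0 |
| Week 16 | 28 | 4 | 2 |
| Week 20 | 32 | 8 | 6 |
| Week 24 | 36 | 12 | 10 |

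The window tied to the end of prophylaxis closes at 12 + 12 = week 24 for a woman who completes the course. Visit 5 meets it, but it gives re-treatment no 12 weeks of its own.

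**The case against.** A reader might infer that the women who tolerate treatment worst disappear from the safety and intention-to-treat data. The protocol does not support that. Any adverse event during the study is registered whether related or not (9.3), is followed until resolved or stable (9.4), and counts in the proportion of women with an event (8.2). The intention-to-treat set is all randomised women, so she stays in it with later outcomes missing; how those are handled may be in the analysis plan, which is not shown.

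Nor does the protocol always equate stopping drug with leaving. Sections 7.2 and 9.4 list stopping or interrupting medication as separate options, Section 7.8 keeps treatment failures in the study, and Section 6.4 is permissive. All of this stands. It narrows the group affected to women removed under 6.4, for whom no section keeps a study visit.

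The primary-endpoint illustration is also open to challenge. It places every removal in one arm, among failures, before Visit 3, and no study culture is scheduled between randomisation and Visit 3 on which failures could be picked out. The base case is close: at one-sided 5% its lower limit is -30.1 by Wald and -29.8 by Newcombe, so whether it misses depends on the method. These objections stand; the table shows only what is possible.

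On the windows, a reader might infer that 12 weeks of registration cannot be delivered, that events after re-treatment mostly go uncollected, or that this too hides poor tolerators. The documents support none of these. The second window fits week 24, the diary and Visit 5 cover re-treatment until then, a long gap arises only when re-treatment ends late, and same-drug re-treatment is offered only to women without adverse events. What remains is that the two windows disagree.

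**Conclusion.** The point holds in a limited form. Women whom the investigator or sponsor removes for adverse events or non-adherence have no study visit retained, which does not fit the promised analysis of all randomised women. The loss concerns later adverse events, cultures, relapses, smears and the Visit 4 biopsy. The epithelial-toxicity and lactobacilli endpoints therefore lean towards women who tolerated treatment; the count of women with an adverse event is largely protected.

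The effect on the primary endpoint is of unknown size, since it needs removal before Visit 3 and the protocol gives no withdrawal rate. Its direction depends on how missing cultures are treated.

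Separately, the two registration windows in Section 9.3 agree without re-treatment but not with it. The first can run past the last contact by 2 to 4 weeks if re-treatment ends at week 16, and by 10 to 12 weeks if it ends at week 24. No re-treatment rate is given. This is a wording conflict to be reconciled, independent of the first matter. Both should be corrected.

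**What to change.** **Section 6.4.** State that stopping study drug for an adverse event or non-adherence does not end study participation. Such women keep Visits 3 to 5 with every assessment they accept, and only withdrawal of consent ends data collection. This concerns data collection only; when drug should be stopped remains a clinical matter.

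**Section 9.3.** Reconcile the two windows. Register adverse events through Visit 5 for every treated woman, whenever drug was stopped. For women re-treated in months 3 to 6, either add a telephone or diary contact so that the stated 12 weeks after the last dose is met, or restate the window so that the last scheduled contact meets it.

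**Figure 1.** Reconcile the week-24 label with Section 5.2, which calls Visit 5 the end of the study.

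**Cost.** Protocol wording, already scheduled visits for the few women off drug and, if the extra contact is chosen, a last contact up to about 12 weeks later for re-treated women.
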